### Data collection

As part of the audit, in addition to screening status and *intention* to attend the screening as described above, the following data will be collected: age, gender, diabetes type, general medical service status, private health insurance, duration of diabetes and treatment type (diet, oral agents, injectables, insulin).

## Process evaluation

### Recruitment

#### General practice staff

All staff at selected practices (GPs, practices nurses and administrators) will be eligible to participate in the process evaluation. A purposive sample of staff who are participating in the study will be contacted by a study researcher following study completion and invited to participate in qualitative interviews.

#### People with diabetes

At study completion, practices will send a letter to, or phone, all eligible patients informing them that the research team is working with their general practice to evaluate a practice approach to promoting screening. Patients who are interested in taking part can provide their contact details to the study team. A member of the research team will then invite them to an interview or focus group and ask them two screening questions (i.e., age and if/when they last attended) to facilitate purposive sampling of participants.

### Data collection

In line with the Medical Research Council guidance [31], a mixed methods approach will be used, involving data collection at the practice, professional and patient level, to assess implementation outcomes, as defined by Procter et al. [58], namely appropriateness, acceptability, feasibility, reach/penetration, fidelity and costs (resource use). A summary is provided below (Table 3) with more detail and definitions available in Table 4.

**Table 3 Tab3:** Summary of data collection

Practice level	
• **Audit;** ongoing data collection (i.e., number of eligible patients, number of reminders delivered) [reach, fidelity]	
• **Research processes;** data collection at study start (i.e., recruitment and retention, briefing attendance and feedback), and via monthly phone calls to practices (i.e., role assignment, changes to the intervention protocol, time and resource use, any feedback) [feasibility, fidelity, costs (resource use)]. Information collected will vary according to timing of the phone call. For example, during the first phone call, the time taken to conduct the audit will be recorded; during the second call, the time needed to deliver reminder phone calls will be recorded***.***	
Professional	
• **Staff questionnaires** at study cessation [appropriateness, acceptability and feasibility]	
• **Staff interviews** at study cessation [acceptability, feasibility and fidelity]	
Patient	
• **Patient interviews or focus groups**, at study cessation [acceptability and fidelity]

**Table 4 Tab4:** Data collection conducted as part of the process evaluation

**Data items**	**Timing**	**Outcome(s)**					
		**Appropriateness**^**b**^	**Acceptability**^**b**^	**Reach**^**b**^	**Feasibility**^**b**^	**Fidelity**^**b**^	**Costs**^**a**^
**Source:** Audit data **Level:** Patient **Content:**				✓		✓	
• Number of patients eligible to receive the intervention	Baseline						
• Number of phone reminders; record on the audit file that (a) patient phoned (and date), (b) spoke to the patient and (c) delivered the scripted message.	On-going						
• Number of letter reminders	On-going						
• Number of in person reminders; review patient files and record whether the electronic alert has been deleted. Deleting the electronic alert will be taken to indicate that the intervention was delivered (self-report).	At 6 months						
**Source:** Research processes **Level:** Practice **Content:**					✓	✓	✓
Recruitment • Recruitment and retention rates, which will be used to inform the sample size calculation for the definitive trial • The time taken to recruit practices, collect data and install the intervention (i.e., training and audit set up) to inform the planning of a larger definitive trial	At recruitment Baseline				✓		
Feedback • Any complaints or feedback about the intervention or research process during the trial	During delivery				✓		
Briefing • Number and type of staff who attend (i.e., practice nurse, GP, administrator); • Time taken to deliver briefing/training; • Participants who attend will be asked for suggestions on how to improve the briefing; • Usual care at the practice, that is, whether they already remind patients, and how this is done at the practice.	During delivery		✓		✓	✓	✓
Researcher phone calls • Staff member assigned to delivery of different intervention components • Why they were assigned to this role • Changes to role assignment and reason for change • Changes to intervention protocol • Any additional resources used to deliver the intervention; for example, additional appointments resulting from the phone call or letter, further phone calls as a follow-up to the original reminder (e.g., ringing the patient back to confirm some detail) • Number of patients who contacted practice for information or came to the practice looking for help with the consent form. • Estimate of the time commitment to the study including time taken to participate in audit and feedback (including verification with programme), incorporate face to face reminders into consultations and to deliver reminder phone calls and issue letters.	Monthly, and reviewed at 6 months				✓	✓	✓
**Method:** Staff questionnaires **Level:** Practice **Content:** • Acceptability of Intervention Measure (AIM) • Intervention Appropriateness Measure (IAM) • Feasibility of Intervention Measure (FIM)	At 6 months	✓	✓		✓		
**Method:** Staff interviews **Level:** Practice	At 6 months		✓		✓	✓	
**Method:** Patient interviews or focus groups **Level:** Patient	At 6 months		✓			✓	

^a^Data collected on resource use, after which monetary values will be assigned to give cost estimates as part of the economic evaluation

^**b**^According to Proctor et al., appropriateness is the ‘perceived fit, relevance or compatibility of the innovation or evidence-based practice for a given practice setting, provider, or consumer and/or perceived fit of the innovation to address a particular issue or problem’**;** Acceptability is the ‘perception among implementation stakeholders that a given treatment, service, practice or innovation is agreeable, palatable or satisfactory’**;** Reach (penetration) is defined as the ‘integration of a practice within a service setting and its subsystems’; Feasibility is defined as the ‘extent to which a new treatment, or an innovation, can be successfully used or carried out within a given agency or setting’ [58]

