#### Remind clinicians

After the audit has been completed, feedback (i.e., a list of patients who have not attended screening) will be used by an assigned staff member to add electronic delivery prompts to the records of eligible patients. This will act as a reminder to prompt professionals (GPs or practice nurses) to deliver the face-to-face reminder message to patients and to record delivery of this message. Health care professionals will be asked to delete the alert if the intervention components (i.e., brief messages, leaflets) were delivered where the functionality to capture action or inaction on the alert exists in the GP software this will be utilised.

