##### Verbal reminders

All eligible patients will receive a phone call from a practice nurse, reminding them to attend the screening. Nurses who deliver the phone call will follow a short script (Additional file 2) and inform the patient they will receive a follow-up letter with more information. At this point, the patient status will also be updated on the audit file and electronic patient record, for example, if the patient is attending another service for screening (e.g., ophthalmologist). This will enable staff to shortlist patients who should receive the letter. In-person reminders will be delivered opportunistically by GPs and practice nurses if an eligible patient attends for an appointment during the 6-month trial period. They will follow the short script (Additional file 2) and provide patients with a standard information leaflet (Additional file 3).

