One limitation is the potential for selection bias. Practices who are interested in improving patient attendance and feel they have the capacity at the practice to do so are more likely to respond to the call for expressions of interest. Many recruitment avenues utilised by the study team are likely to be populated by professionals with an existing interest in research and quality improvement, who may have better systems and processes in place, making it more feasible for them to deliver the IDEAs intervention. A further limitation is that information on research processes provided by practice staff (as part of monthly phone calls), and fidelity as relayed during interviews at study completion, could be subject to recall and self-report biases. Electronic alerts may be deleted by professionals regardless of whether they have delivered the in-person reminder. It is not within the scope of the study to modify practice software to capture action or inaction on the alert, unless this functionality already exists. Measuring resource use for the economic evaluation relies on the accuracy of staff recall, specifically the time taken to deliver components, and whether additional resources were used. However, an observational time-in-motion study would be inappropriate given confidentially concerns and the potential to breach the General Data Protection Regulations (GDPR).

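### In-person reminders are counted from deleted alerts, but the deletion instruction is not limited to face-to-face delivery, so the in-person reach and fidelity count is unreliable

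*Protocol article*

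**What the plan says.** - **How the count is made.** In Table 4 (Process evaluation, Data collection), the item on in-person reminders tells staff at 6 months to "review patient files and record whether the electronic alert has been deleted". The rule for reading the result is "Deleting the electronic alert will be taken to indicate that the intervention was delivered (self-report". The audit block that holds this item is ticked for reach and fidelity.
- **What staff are told.** Under Remind clinicians, the audit list "will be used by an assigned staff member to add electronic delivery prompts to the records of eligible patients". The prompt is meant to get professionals "to deliver the face-to-face reminder message to patients and to record delivery of this message". The deletion instruction follows: "Health care professionals will be asked to delete the alert if the intervention components (i.e., brief messages, leaflets) were delivered". Software that logs action or inaction on the alert is to be used where a practice already has it.
- **What else reaches the patient.** Reminders come after prompts have been added (Intervene with patients). A nurse is to phone every eligible patient, and after the call "the patient status will also be updated on the audit file and electronic patient record" (Verbal reminders). A letter enclosing the leaflet follows. Calls and letters fall in the two weeks after the audit, whereas opportunistic reminders run through the 6-month trial period. Table 2 lists one laminated script for both phone and face-to-face encounters.
- **How phone reminders are counted.** Staff "record on the audit file that (a) patient phoned (and date), (b) spoke to the patient and (c) delivered the scripted message" (Table 4).
- **What is conceded.** The Discussion says: "Electronic alerts may be deleted by professionals regardless of whether they have delivered the in-person reminder". It adds that changing practice software is out of scope.

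**The concern.** The alert has two jobs: it prompts the face-to-face reminder, and its removal serves as evidence that the reminder took place. The second job works only if nothing except a face-to-face reminder leads to deletion, and the text does not secure that. A nurse who gives the scripted message by phone, sees the leaflet posted and then clears the alert has arguably followed the instruction as written. Table 4 would record an in-person reminder that never happened. The Discussion does not cover this route; it concedes deletion without delivery, not deletion after delivery by another channel.

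Clearing the alert in the first weeks also takes away the prompt for the rest of the 6 months, so it may lower true in-person delivery while raising the recorded figure.

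At stake is the description of one distinct patient-level component. Whether the intervention is delivered as intended is one of the study's stated questions, and the findings are to be used to refine the intervention. A reach figure that mixes phone, letter, dismissal and in-person contact cannot inform that refinement.

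**Working it through.** The plan states no figure for this count, so there is nothing to reproduce. The check sets the passages side by side and then shows how far the count could move.

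**Step 1. What a deleted alert can mean**

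| Event | Consistent with the deletion instruction? | Counted in person by Table 4? | True in-person reminder? |
|---|---|---|---|
| Message and leaflet given face to face, alert deleted | Yes | Yes | Yes |
| Message by phone, leaflet by post, alert deleted | Yes, as worded | Yes | No |
| Alert dismissed, nothing delivered | No (conceded in the Discussion) | Yes | No |
| Given face to face, alert left in place | No | No | Yes |

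Rows 2 and 3 inflate the count; row 4 deflates it. The status update after the phone call is a further plausible occasion for clearing, but the protocol does not say the alert is removed then.

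**Step 2. Size, by illustration**

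Let d be the true proportion reminded in person, s the probability that the alert is deleted given in-person delivery, and f the probability that it is deleted without in-person delivery. Then

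recorded proportion = d × s + (1 − d) × f.

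All three rates are assumptions. For patient numbers, the Sample size section expects 18 eligible patients per practice, so four intervention practices give 4 × 18 = 72.

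With d = 40% (28.8 of 72 patients):

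| s | f = 0% | f = 10% | f = 30% | f = 50% |
|---|---|---|---|---|
| 100% | 40% | 46% | 58% | 70% |
| 80% | 32% | 38% | 50% | 62% |
| 60% | 24% | 30% | 42% | 54% |

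Example: s = 100%, f = 30% gives 0.40 × 1 + 0.60 × 0.30 = 0.58, that is 72 × 0.58 = 41.8 patients recorded against 28.8 true. Over this table the error runs from −16 to +30 percentage points.

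**Step 3. Direction**

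The count is too high only when (1 − d) × f > d × (1 − s).

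- d = 40%, s = 80%: f must exceed 0.08 / 0.60 = 13.3%.
- d = 40%, s = 60%: f must exceed 0.16 / 0.60 = 26.7%.
- d = 60%, s = 60%: f must exceed 0.24 / 0.40 = 60%, so for f from 0 to 50% the count is too low throughout (36% to 56% recorded against 60% true).

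The sign therefore depends on rates that the pilot, as planned, does not measure.

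**Step 4. Route into the continuation decision**

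The Table 1 implementation criterion is scored as the share of practices that delivered the core components (audit, prompts, reminders), and a reminder in any format suffices. A patient wrongly credited with an in-person reminder after a phone call or letter has already been reminded in another format, so the false credit changes nothing there. The listed measure of the percentage of eligible patients receiving the intervention also draws on audit data, but the same overlap with phone and letter limits the effect.

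**The case against.** The strongest reply is that the alert is tied to face-to-face delivery by the sentence before the deletion instruction, which also asks professionals to record that delivery. Existing software logging will be used where available, the measure is labelled as self-report, and dismissal is openly listed as a limitation. Fidelity is also explored through monthly calls and through staff and patient interviews. In-person reminders are one descriptive sub-count on top of phone and letter reminders.

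Much of this stands. Dismissal is disclosed, and the context does suggest face-to-face use. But the deletion instruction itself names messages and leaflets without a channel, and both are also delivered by phone and post. Table 4 does not say that it uses the requested delivery record. Software logging helps only some practices. Calls and interviews give no count per patient, and the Discussion itself notes their recall and self-report bias.

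Three stronger readings are tempting, and the documents do not support them:

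- A reader might infer that an alert never added counts as delivered, so that a practice placing no alerts would score 100%. Table 4 speaks of deletion, not absence, and adding prompts is assessed as its own component. The miscount arises only if the file reviewer cannot tell the two apart. No dated record per patient of adding the alert is described, so this is possible, but it is inference.
- A reader might infer that reach and fidelity are necessarily overstated. Alerts left in place after delivery pull the count down, and Step 3 shows that either sign is possible.
- A reader might infer that the go/no-go decision is compromised. Step 4 shows why the effect there is small.

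**Conclusion.** The point holds as a measurement problem confined mainly to the in-person count. Table 4 treats a deleted alert as an in-person reminder, while the deletion instruction allows clearing after delivery by another channel. The resulting reach and fidelity figure for this component is unreliable, with overstatement plausible but not certain. The illustrated error of −16 to +30 points rests on assumed rates (true delivery 40%, deletion after delivery 60% to 100%, deletion without in-person delivery 0% to 50%); the documents supply none of them. The practice-level continuation decision is little affected. The change is worth making because it is cheap and the protocol already contains the parts needed.

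**What to change.** 1. Count an in-person reminder only from a dated entry per patient on the audit file (message given, leaflet given), parallel to the phone entry and drawing on the delivery record that Remind clinicians already requests.
2. Record on the audit file the date each alert was added, so that an alert never placed cannot be confused with one deleted.
3. Reconcile Remind clinicians with Table 4 by stating whether delivery by phone or letter permits the alert to be cleared.
4. Report alert deletion without an entry separately, as a secondary and unconfirmed indicator.

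The cost is a brief extra entry per consultation and a few audit columns. No software change is needed, so the stated scope limit is respected. The entry is still self-report, and some delivered reminders will be missed when it is forgotten, so the reported in-person reach may be lower.

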#### Audit data and research processes

The staff member responsible for the audit will record the number of patients eligible to receive the intervention and the number of reminders delivered. The researcher who delivers the briefing and training will record information on attendees, time required, usual care at the practice and ask for suggestions on the delivery and content of the briefing. Information from monthly phone calls will be recorded on a standardised extraction form.

#### Staff questionnaires

At study completion (6 months), staff at participating practices will be asked to complete a questionnaire containing three previously validated measures, to assess the acceptability, appropriateness and feasibility of the intervention [59]. Acceptability is defined the ‘perception among implementation stakeholders that a given treatment, service, practice or innovation is agreeable, palatable or satisfactory.’ Appropriateness is the ‘perceived fit, relevance or compatibility of the innovation or evidence-based practice for a given practice setting, provider or consumer and/or perceived fit of the innovation to address a particular issue or problem’. Feasibility is defined as ‘the extent to which a new treatment, or an innovation, can be successfully used or carried out within a given agency or setting’ [58, 59]. Practice staff will also be able to provide additional comments on the intervention, specifically the fidelity, acceptability, suitability and/or comprehensiveness of the study and intervention procedures, and how these might be improved.

#### Staff interviews

A purposive sample of staff (GPs, practice nurse, practice manager, administrator) will be invited to participate in semi-structured interviews. The initial sample will comprise 12 staff members (one GP, practice nurse and administrator or manager from each of four intervention practices). Drawing on the principles of theoretical saturation and data saturation [60–62], data will be analysed at this point. Saturation will be judged at the practice level. Therefore, further sampling may be directed to pursue new topics arising which are specific to one practice. Where numbers allow, three further interviews with different staff members (one GP, nurse and administrator/manager) will be conducted to determine whether new topics within the main implementation constructs, acceptability and feasibility, arise. If necessary, further interviews will be conducted in blocks of three.

Topic guides will be informed by existing implementation frameworks to explore key constructs, including but not limited to the Theoretical Framework of Acceptability [63], Consolidated Framework for Implementation Research [64] and the Framework for Reporting Adaptations and Modifications-Enhanced (FRAME) [65, 66]. Interviews will explore staff members’ perspectives and experiences of the intervention and research procedures, fidelity to the intervention process (delivered as planned or whether adaptations to the intervention were made during delivery) and the overall feasibility and acceptability of the study procedures and the intervention, including strengths and weaknesses of the intervention, and key challenges (barriers and facilitators) to implementation in practice. Beliefs about the capacity and resource need to deliver the intervention, training needs and contextual influences on implementation will be explored. Data collection and analysis will be iterative. A separate consent will be obtained from staff who participate in the end of study interviews.

#### Patient interviews or focus groups

Interviews will also be carried out with patients with type 1 or type 2 diabetes who received the patient-level intervention. A purposive sampling strategy will be used to recruit participants from intervention practices (2–3 patients from each practice) on the basis of age, sex and attendance pattern (i.e., never attender, recent attender). A semi-structured topic guide will be used to elicit feedback on their experiences and perspectives of the intervention, whether the intervention was acceptable, advantages and disadvantages, and the perceived influence on behaviour. The topic guide will be informed by previous literature on barriers to screening attendance [29], and the theoretical basis for how the intervention is expected to work. If it is unfeasible to arrange focus groups, or if patients are unable to attend, then they will be given the option to take part in an interview. At the start, patients will be asked to complete a short 6-item questionnaire, asking them their age, how long they have diabetes, the type of diabetes, their occupation, whether someone in their family has diabetes and if they have any existing diabetes-related complications either now or in the past. Patients will not be obliged to complete the questionnaire to participate in the focus group or interview.

